## 4.3.7 Study variables

- Maternal homecare practices
  - Nutritional requirements
  - Initiation of ANC attendance
  - Birth preparations
  - Exertion during pregnancy
- Neonatal home care practices
- Care during delivery
  - Care for the cord (cutting and cleaning)
  - Warmth for the newborn
  - Initiation of breast feeding
  - Provision of pre-lacteal feeds
- Harmful maternal and newborn practices
- Healthy maternal and newborn practices

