### 4.3.6 Sampling procedure

For the quantitative survey, clusters will be stratified at the parish level; a list of all parishes will be obtained from the planning unit of the districts and 21 of them will be selected by a simple random technique using computer generated random numbers. At the parish level all lactating women with babies up to four months will be enumerated and a list generated. From this list a random sample proportionate to the total number will be identified and included in to the study. A written consent will be obtained from each participating lactating woman. Structured interview questionnaire (*see annex 6 for details*) will be administered by trained research assistants to all lactating women who provide consent to participate in the study.

This study will be conducted in Masindi and Kiryandongo districts in western Uganda. The questionnaire guide will be pre-tested twice to ensure suitability.

In the qualitative study, six elderly caregivers and six traditional birth attendants will be identified with the help of Local council I chairpersons or their representative from any of the 21 parishes sampled. Thirty lactating mothers stratified by age groups (adolescents 10-20 years and adults above 20 years) will be selected for In-Depth Interviews. All these will be individual interviews with open-ended questions. Written informed consent will be obtained from participants and the interview administered on acceptance (*see annex 7 for details of question guide)*. While we plan to interview a total of six elderly care givers and six TBAs the absolute number will be determined when we arrive at saturation point-when no more new practices and explanations are volunteered in subsequent interviews.

For the quantitative survey, lactating mothers having babies up to sixty days old (about two months) will be eligible for the study (see annex 5 for sampling procedure). The unit of analysis will be individual lactating mothers.

The number of lactating mothers to be interviewed per cluster will be allocated proportionate to the number of eligible lactating mothers available in the selected parishes.

Eligible lactating mothers will be identified by the use of village-bicycle scouts assisted by the local council I chairpersons (LC I) who will enumerate all eligible lactating mothers and generate a list; from this list a proportionate number from each of the parishes will be sampled using a simple random selection technique.

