**A: Socio-demographic characteristics**

1. Code number..........................................................................................
2. Name of household Head........................................................................
3. Age of Respondent in completed years (lactating woman)....................
4. Parity of respondent 1, 2, 3, 4, 5, over 5
5. Highest education level attained:
6. Non
7. Primary;
8. Secondary;
9. High school;
10. Tertiary;
11. Marital status:
12. Married
13. Single
14. Separated
15. Divorced
16. Widowed
17. What do you do for a living:
18. Nothing
19. Housewife
20. Farming/gardening
21. Selling in the market/petty trade
22. Business woman
23. Salaried
24. Did you attend any ANC during the last pregnancy:
25. Yes, 2. No
26. Number of ANC visits made with the last pregnancy:
27. 0,
28. 1,
29. 2,
30. 3,
31. 4
32. More than 4
33. Where did this last delivery take place:

**1)** Home;

**2)** Health facility;

**3)** On the way to health Facility

1. How old is the baby now? Age in completed weeks
2. 0-1 week **2)** 2-4 weeks **3)** 5-8 weeks **4)** 9-13 weeks
3. Number of living children: 1, 2, 3, 4, 5, 6, more than 6
4. Number of deceased children: 0,1, 2, 3, 4, 5, 6, more than 6

(*if deceased babies is* ***0*** *then skip to section* ***B***)

1. At what ages did the deceased children die?

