**B: Data on the last pregnancy**

1. During your last pregnancy is there any food that was forbidden for you to eat?

1=Yes

2=No

1. If YES why?

1) will make the baby grow too big

2) will cause the baby to come out;

3) other, Specify...................

1. During this pregnancy were you advised not to take part in certain activities?

1=Yes

2=No

1. If YES, please *(circle all that apply)*:

1) Not going to the well to fetch water

2) Not using a pit latrine

3) Not engaging in sexual intercourse

4) Other, please Specify...................

1. Did you make any preparation for this delivery?

1=Yes

2=No

1. If YES, what specific preparations did you make? *(Circle all that apply)*

**1**) Secured warm dresses and other items for the baby like basin,

**2**) mama kit, mackintosh,

**3**) saved some money,

**4**) decided where to deliver from,

**5**) selected a caretaker for the remaining children while I am away ,

**6**) other, please specify

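### Sub-study two lists initiation of antenatal care as a variable, but its questionnaire never asks when care began; nutrition and exertion are covered only as restrictions and advice

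*Protocol*

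**What the plan says.** Section 4.3.7 names four maternal homecare variables and defines none of them: "Nutritional requirements", "Initiation of ANC attendance", "Birth preparations" and "Exertion during pregnancy".

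Section 4.3.6 fixes the instrument for the quantitative survey: "Structured interview questionnaire (*see annex 6 for details*) will be administered by trained research assistants".

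On these topics Annex 6 asks the following:

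- Section A: whether any antenatal care was attended, and the "Number of ANC visits made with the last pregnancy", coded from none to more than four.
- Section B, food: "During your last pregnancy is there any food that was forbidden for you to eat". A follow-up asks why, with two coded reasons and an open category.
- Section B, activity: "During this pregnancy were you advised not to take part in certain activities". A follow-up lists fetching water, using a pit latrine, sexual intercourse and an open category.
- Section B, preparation: whether the woman prepared for the delivery and, if so, which preparations she made.

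Section 4.3.8 plans to report proportions and rates, and to test associations between socio-demographic characteristics and the maternal and newborn care practices.

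**The concern.** A variable that the plan sets out to quantify needs a question behind it. For initiation of antenatal care there is none. Late initiation is one of the problems on which the protocol rests its case: section 1.4 cites the share of women who first attend in the first and third trimesters, section 2.3 returns to late first visits, and section 4.4.6 justifies the trial's 28-week limit by when women first attend. Followed as printed, the community survey would say nothing about that timing in Masindi and Kiryandongo. It also could not test which women start late, although section 4.3.8 plans determinant analyses.

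For nutrition and exertion the stakes are lower. The questionnaire records restrictions and advice, while the variable names could be read as diet and workload. Unless the definition is settled, a report could present a food-taboo proportion as a finding on maternal nutrition.

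**Working it through.** **Survey size (context only; no figure is disputed).** Section 4.3.5 gives Z = 1.96, P = 0.42, Q = 0.58, design effect 2, sampling error 0.05 and 40 women per cluster.

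- Clusters: 1.96² × 0.42 × 0.58 × 2 / (0.05² × 40) = 18.716; the protocol states 18.7.
- Women: 18.7 × 40 = 748, as stated.
- With 10% added for non-response: 748 × 1.1 = 822.8; the protocol states 823.
- Clusters for 823 women: 823 / 40 = 20.6, rounded up to 21, as stated.

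So the survey is sized to estimate a prevalence of 42% to within 5 percentage points. That precision exists only for variables that have an item.

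**Mapping the four variables in section 4.3.7 to the items in Annex 6.**

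| Variable | What Annex 6 records | What it does not record | Result |
|---|---|---|---|
| Initiation of antenatal care | Any attendance; number of visits | Month, trimester or gestation at first visit | Not measured |
| Nutrition | Any food forbidden; reason | Which food; whether the woman complied; what she ate | Thin |
| Exertion | Any activity advised against; which | Work actually done | Thin |
| Birth preparation | Whether made; which | – | Covered |

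The count is 1 of 4 not measured, 2 of 4 thinly covered and 1 of 4 covered.

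**Does initiation mean timing?** Section 4.3.7 does not define it, but the protocol's usage is consistent. Section 1.4 speaks of initiating care by trimester and of late initiation. Section 4.4.6 speaks of early initiation in relation to the first trimester. Reading it as ever attending would leave the word with no content beyond the attendance question.

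**Can timing be recovered from the visit count?** No. A count of zero identifies a woman who never started. A count of one fits a first-trimester visit or a visit in the last month equally well, and higher counts do not fix the start either.

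**Does another tool in the sub-study supply it?**

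- Annex 7, for birth attendants and elderly caregivers, asks about forbidden foods and tasks but not about the first antenatal visit.
- Annex 8 puts three broad open questions to 30 lactating women and cannot yield a prevalence.
- Section 4.3.4 lets themes from the key informant interviews be added to the questionnaire. Nothing in the Annex 7 guide would lead to timing.

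**How thin are the exertion codes?** Of the three named activities, only fetching water is clearly physical exertion. Other work could appear only through the open category.

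**The case against.** The strongest reply concerns nutrition and exertion, and most of it stands. The operational definitions treat homecare practices as care given at home according to what caregivers know and believe, and section 4.3.9 describes the survey data as practices received by the mothers. Foods forbidden and activities advised against fit that construct. A reader might infer that three of the four maternal variables cannot be derived, or that 823 interviews yield no estimate for them. The documents do not support that. The proportion told to avoid a food, the reasons, and the proportion advised against each activity can all be tabulated. Annex 7 also asks which foods are forbidden, and section 4.3.4 allows such themes to enter the survey.

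A second reply is that the trial does not depend on these estimates. That is also largely right. The educational procedure in Annex 15 has the counsellor ask each woman about food, prohibited foods, work and help, and it records gestation at her first visit. Section 4.4.6 cites a district figure of about 45% first attending in the second trimester. None of the three variables is a trial outcome in section 4.4.7. However, the trial's own records cover only women enrolled at up to 28 weeks in selected health centres. They therefore cannot show the community distribution of first-visit timing, and least of all the late starters.

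A third reply is that a more consequential gap lies in the same list: section 4.3.7 names initiation of breastfeeding and pre-lacteal feeds, and the printed Annex 6 has no item on either. That is a separate matter and does not weaken this one.

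None of these replies supplies the timing of the first antenatal visit.

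**Conclusion.** The point holds for initiation of antenatal care: a listed survey variable has no item that measures it, and the survey as written cannot estimate it at any sample size. For nutrition and exertion the point is narrower. The items give estimates of restrictions and advice, not of diet or work done, and the variable names do not say which is meant.

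The conclusion rests on three assumptions: that initiation means timing of the first visit, as the rest of the protocol uses it; that Annex 6 as printed is complete on these topics, its sections running in order from A to H; and that it would be fielded without further items. A statistical analysis plan could not repair the omission, because the data would not have been collected. The consequence falls on sub-study two's description of practices and their determinants, not on the trial's outcomes.

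**What to change.** Before the two planned pre-tests, make three changes.

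1. Add to Annex 6 an item on the gestational month or trimester at the first antenatal visit, taken from the antenatal card where the woman holds one and from recall otherwise, with the source recorded.
2. Add a follow-up to the forbidden-food question asking which food.
3. For nutrition and exertion, choose one route and state it in section 4.3.7: either define the variables as food and activity restrictions received, which the existing items measure, or add a short item on foods eaten and work done and keep the existing items as advice received.

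The first two changes and the redefinition cost two questions and an edit to section 4.3.7. The fuller route adds one or two more questions. The downside is a slightly longer interview for each of the 823 women.

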## 4.3.8 Data collection and analysis plan

For both qualitative and quantitative data collection techniques research assistants familiar with the local dialect (Runyoro, Luo and Kiswahili) and possessing at least a degree in social sciences or public health having experience in social research will be recruited and trained for three days on the use of available tools and techniques. Pre-testing will be done twice to ensure suitability of the tools. Qualitative data from the Key Informant Interviews with elderly caregivers, TBAs and lactating women will be audio taped, transcribed verbatim and translated in to English, themes regarding prenatal and newborn homecare practices will be identified and described. A detailed description of the different care practices will be explored from elderly care givers and TBAs; these practices will be elaborated and broadly categorised according to prenatal, intra- and post-natal periods. The computer software program NVivo will be used. We will use content analysis to analyse data from TBAs and elderly caregivers and lactating mothers. Analysis will focus on making a detailed description of maternal and newborn care practices and the rationale for these care practices in the homes. For the In-Depth Interviews manual analysis of experiences of the different age groups adolescents (young adolescent ages 10-13 years; middle age 14-16 years and older adolescents ages 17-20) and older women over 20 years will be considered.

In the quantitative data with lactating mothers research assistants will be recruited and trained on the use of data collection tools; questionnaires will be pre-tested twice to ensue suitability of data collection tool; double data entry will be done in *epidata version 3.02*, cleaned and exported to *stata version 10.0* for analysis. Results will be presented in terms of descriptive statistics in proportions and rates. In a second level using bivariate data analysis, we will test for association between socio-demographic characteristics and the different maternal and newborn care practices using odds ratios and confidence intervals to test for levels of significance.

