**Methodology**: This study will be done in Masindi and Kiryandongo districts in western Uganda. We plan to conduct three sub studies: Sub study one, a descriptive cross-sectional study with healthcare workers and health managers; using structured questionnaires, Focus Group Discussions and Key Informant Interviews. Sub study two is a cross-sectional population based observational study targeting lactating women, traditional birth attendants and elderly caregivers; using Key Informant Interviews with TBAs and Elderly caregivers, In-Depth Interviews and Structured Interviews with lactating mothers. Sub study three a community intervention trial allocating health centres to two different arms (routine ANC care only; routine ANC care and CHWs offering standardized prenatal education at the primary care facility plus standardized mobile phone reminders through CHWs).

**Statistical analysis plan**: Qualitative data will be audio taped, transcribed verbatim, translated in to English and analysed for emerging themes. Quantitative data will be entered in to Epidata 2002 computer software package, cleaned and exported to stata version 10.0 for analysis. Data on knowledge and perception of health workers together with data on common maternal and newborn homecare practices will inform the design for sub study three. In sub study three we will measure timely return ANC visits, completed antenatal care visits, number of institutional deliveries and homecare practices in the two arms. Analysis will be done in stages: univariate to generate frequencies, bi-variate analysis will be done to establish associations between variables of interest. Chi-square tests will be used to establish significant associations; at the Multivariate level, analysis will be run to get Odds Ratio values, 95% CI for the OR and the respective p-values will be presented.

**Dissemination and utilisation**: Results of this study will be shared and discussed with district local authorities and the Ministry of health officials; presentations will be made in national and international conferences and; publications in peer reviewed journals. These findings will specifically inform the ongoing debate on antenatal care service improvement and contribute to the attainment of MDGs 4 and 5.

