# 4.3 Sub-study two

**Prevalence of common pre-and neo-natal homecare practices their rationale and determinants among communities of Masindi and Kiryandongo districts in Western Uganda**

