## 4.3.3 Specific objective

1. Determine the common pre-and neo-natal homecare practices and their determinants among lactating women in Masindi and Kiryandongo districts
2. Investigate the rationale for the different homecare practices offered to pregnant women and newborn babies during the pre-,intra- and immediate post-natal period in the districts of Masindi and Kiryandongo
3. Explore homecare experiences received by lactating women during the pre-and neo-natal period in the district of Masindi and Kiryandongo

##

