**4.4.10 Data management and analysis**

At the end of each trail day, data will be collected, sorted and checked for consistency and for completeness. Open-ended questions will be categorized. All data collected will be entered in Epi-data soft ware package and exported to stata 8.2 soft ware package for more analysis. This analysis will be done in stages: univariate analysis ,where frequencies of variables will be generated and tabulated to establish the extent of use of these ANC services in the standard health centre setting compared to the second arm where extra education, and telephone remainders will be made. This level will also show the factors influencing timely return ANC visits, completion of the four recommended ANC visits, institutional deliveries and newborn care practices (Provision of warmth to the newborn, Initiation of breastfeeding within one hour of birth, Care for the cord and Immunization for the newborn-Polio 0 & 1; BCG within the neonatal period). At bi-variate level of analysis, cross tabulations will be run to establish associations between variables of interest. Chi-square tests will be used to establish significant associations. At multi variate analysis, all variables that will be found to be statistically significant at bi-variate ,will be subjected to the multivariate model (logistic) to control for confounding. The analysis will be run to get Odds Ratio values, 95%CI for the OR, and the respective p-values will be presented. Finally the primary outcomes of interest will be compared between the two arms i.e. a standard arm and the new trial arm upon which conclusions will be drawn.

*Quality Control*

To control quality of data to be collected,(completeness, correctness and consistency), the following measures will be undertaken:

Research assistants will be selected and trained by the principal investigator, questionnaires will be pre-tested for one day in a few selected health centres in Masindi and Kiryandongo. Completed questionnaires will be collected and checked by the principal investigator. Data collection will be carried out under strict supervision of the principal investigator. Data editing will be done and corrections will be made there at the selected health centres.

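### Sub-study two promises determinants of homecare practices but plans only bivariate odds ratios, so each socio-demographic association is open to confounding by the others

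*Protocol*

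**What the plan says.** The title of sub-study two (Protocol 4.3) announces "Prevalence of common pre-and neo-natal homecare practices their rationale and determinants among communities of Masindi and Kiryandongo districts". Specific objective 1 (4.3.3) is to "Determine the common pre-and neo-natal homecare practices and their determinants among lactating women in Masindi and Kiryandongo districts", and the summary table in 4.3.9 repeats it. The introduction (4.3.1) also lists determinants among the things the survey will examine.

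Section 4.3.8 sets two quantitative levels. First, "Results will be presented in terms of descriptive statistics in proportions and rates". Then, "In a second level using bivariate data analysis, we will test for association between socio-demographic characteristics and the different maternal and newborn care practices", done "using odds ratios and confidence intervals to test for levels of significance". The section ends there, with no adjusted model.

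Sub-study three is handled differently. In 4.4.10, variables significant at the bivariate stage "will be subjected to the multivariate model (logistic) to control for confounding". The Abstract also has an adjusted stage: "at the Multivariate level, analysis will be run to get Odds Ratio values". It comes after the sentence that introduces the sub-study three measurements.

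**The concern.** A determinant is normally understood as a characteristic related to the practice once the other characteristics are taken into account. A crude odds ratio does not separate age from parity, or education from occupation. Annex 6, section A, records all of these together with marital status. Analysed one at a time, a characteristic with no relation of its own can look important because it travels with one that has, and a real one can be masked.

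At stake is the determinants half of objective 1. The prevalence half is answered by the planned proportions. The protocol accepts the need to adjust in sub-study three but does not carry it into 4.3.8, so objective and analysis do not match within sub-study two.

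**Working it through.** **The plan's own figures (4.3.5).** Clusters = Z²PQD/(δ²b), with Z = 1.96, P = 0.42, Q = 0.58, D = 2, δ = 0.05 and b = 40:

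- 3.8416 × 0.42 × 0.58 × 2 / (0.0025 × 40) = 18.7 clusters, as stated.
- 18.7 × 40 = 748 women, as stated.
- 748 × 1.10 = 822.8, or 823; 823/40 = 20.6, or 21 clusters, as stated.

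These reproduce. The point does not depend on them, except that 823, 748 and D = 2 are used below.

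**How large could the confounding be?** The documents give no correlations between the characteristics, so every input here is an assumption, apart from the sample sizes and D:

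- Good cord care is 37% in women with lower education. Secondary education has an odds ratio of 2: the odds are 2 × 0.37/0.63 = 1.175, which gives 54.0%.
- Occupation (salaried or trading against farming) has no effect of its own.
- The 823 women split 30/70 by occupation: 247 and 576.
- 20% of farmers have secondary education. The share among salaried or trading women varies from 30% to 60%.

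Strongest case, 60% v 20%:

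- Salaried or trading: 0.6 × 0.540 + 0.4 × 0.37 = 47.2%.
- Farming: 0.2 × 0.540 + 0.8 × 0.37 = 40.4%.
- Crude odds ratio = (0.472/0.528)/(0.404/0.596) = 1.32, although the true adjusted value is 1.00.
- Overall prevalence = 0.3 × 47.2% + 0.7 × 40.4% = 42.4%, in line with the plan's P of 42%.
- SE of the log odds ratio = √[1/(247 × 0.472 × 0.528) + 1/(576 × 0.404 × 0.596)] = 0.153.
- z = 0.277/0.153 = 1.81. The chance of p < 0.05 is Φ(1.81 − 1.96) + Φ(−1.81 − 1.96) = 44%.
- With the SE multiplied by √2 for D = 2, z = 1.28 and the chance is 25%.

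The same steps with weaker correlation:

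| Secondary education by occupation | Crude OR for occupation | Chance of p < 0.05 | With D = 2 |
| --- | --- | --- | --- |
| 60% v 20% | 1.32 | 44% | 25% |
| 50% v 20% | 1.23 | 27% | 16% |
| 40% v 20% | 1.15 | 15% | 10% |
| 30% v 20% | 1.07 | 7% | 6% |

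An unconfounded test would give 5% in each row. With 748 responding women instead of 823, the top row becomes 41% and 23%.

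**Does the Abstract already supply the step?** Its staged analysis follows the sub-study three sentence and has the same three stages as 4.4.10: frequencies, bivariate analysis with chi-square tests, then a multivariate stage giving odds ratios, confidence intervals and p-values. Section 4.3.8 mentions neither chi-square tests nor a third stage. The natural reading ties the Abstract's stages to sub-study three.

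**The case against.** The strongest reply is that the adjusted step may already be there. The Abstract's analysis paragraph opens with quantitative data in general and names Stata 10.0, the version in 4.2.9 and 4.3.8, whereas 4.4.10 names Stata 8.2. Section 4.3.8 speaks of a second level without calling it the last, and a separate analysis plan, not available here, could add a model. The ambiguity is real. But if the Abstract does cover sub-study two, it conflicts with 4.3.8, which states its own method and stops at the bivariate step. Either way the text needs correcting.

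Two stronger conclusions are tempting. A reader might infer that each crude odds ratio is in fact confounded and that objective 1 will be answered wrongly. The documents give no correlations to show this, and under weak correlation the distortion is close to nil. A reader might also infer that the trial's education messages would be misdirected. Section 4.3.1 does list determinants among what will inform them, but the general objective (4.3.2) and the Abstract rest on the practices themselves, and the procedure in Annex 15 takes every woman through the same topics, adapted to her own history. No message is assigned by education or occupation group.

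It is also fair to say that adjustment does not by itself identify determinants. Occupation may follow from education, and parity from age. A mutually adjusted coefficient can then hide part of a real effect.

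**Conclusion.** The point stands as a mismatch between objective and method. Sub-study two undertakes to find determinants, while 4.3.8 provides only crude associations that are open to confounding. The determinants part of objective 1 may therefore be misanswered, and nothing in 4.3.8 would reveal whether it had been.

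The size is uncertain. On the assumptions above, the chance of a falsely significant occupation effect is about 7% to 44%, or about 6% to 25% with D = 2, and slightly lower with 748 women. The upper figures need a strong link between education and occupation and should not be quoted alone. The prevalence estimates, the sample size and the trial's primary comparison are untouched. This is a worthwhile, inexpensive improvement to a formative survey.

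**What to change.** Add a paragraph to 4.3.8:

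- Fit one multivariable logistic model per practice, with a covariate list fixed in advance from Annex 6: age, parity, education, marital status and occupation.
- Use standard errors clustered by parish. The sample size assumes D = 2, yet 4.3.8 does not mention clustering. If that design effect applied to a comparison and were ignored, a nominal 5% test would reject a true null about 17% of the time: 2 × [1 − Φ(1.96/√2)].
- Report crude and adjusted odds ratios side by side.
- Interpret the adjusted coefficients with regard to which covariates may lie on a pathway, for example occupation after education, parity after age, and place of birth.

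If the sponsor prefers not to adjust, the minimum is to describe the results as unadjusted associations in 4.3, 4.3.1, 4.3.3 and 4.3.9, and to state in the Abstract which sub-study its multivariate stage covers.

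The cost is a little more analysis work and somewhat wider intervals. No new data are needed, and the planned sample size does not change.

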### 4.3.5 Sample size and technique

The formulae for cluster surveys will be used to estimate the maximum number of clusters and sample size. Using the formula,

C= [Z^2^PQ] D/$\delta^{2}b]$ Where,

- Z, the standard normal deviate at 95% confidence which is 1.96
- P, the prevalence of homecare practices in the region taken to be 42% (0.42) [good cord care ([Waiswa P, Stefan P et al. 2010](#_ENREF_99))]
- Q, (1-p) is 0.58
- D, the design effect taken to be 2,
- $\delta$, a sample error of 5%
- b, the average number of individuals to be sampled per cluster = 40 (derived from 4.85% of expected deliveries per population),

Substituting, the number of clusters needed for the survey is 18.7, implying that a minimum sample size of 748; adjusted for 10% non response we will recruit 823 participants from 21 clusters (see annex 5).

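### Sub-study two is sized as a cluster survey with a design effect of 2, but its analysis section does not carry the parish clustering into the standard errors

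*Protocol*

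**What the plan says.** Protocol section 4.3.5 sizes the survey with a cluster-survey formula: "D, the design effect taken to be 2", with "b, the average number of individuals to be sampled per cluster = 40". The result is that "the number of clusters needed for the survey is 18.7, implying that a minimum sample size of 748", raised to 823 women in 21 clusters for non-response.

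Section 4.3.6 takes parishes as the clusters: "21 of them will be selected by a simple random technique using computer generated random numbers". Women are then sampled within each parish, and the individual lactating mother is made the unit of analysis. Annex 5 adds a stage of three villages per parish.

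Section 4.3.8 gives the quantitative analysis: double entry, export to Stata, description by proportions and rates, then bivariate tests of socio-demographic characteristics against care practices, "using odds ratios and confidence intervals to test for levels of significance". It does not mention clustering, survey estimation, robust standard errors or random effects. Neither does the statistical paragraph in the Abstract.

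**The concern.** The sample size recognises that women in the same parish resemble one another. The analysis section does not. An analyst who follows 4.3.8 as written would run individual-level commands, and the allowance that was paid for in recruitment would be lost in the standard errors.

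Prevalence comes first, because it is the quantity on which the survey is sized. An interval computed as if the women were independent would claim more precision than section 4.3.5 says the survey has. The determinants come second: section 4.3.3 makes them an objective, and 4.3.8 uses intervals as significance tests, so understated standard errors could present chance associations as determinants. Section 4.4.1 says that the community survey is a basis for the educational messages of the trial. The trial's own analysis is in 4.4.10, so a change there would not correct this one.

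**Working it through.** **Inputs from section 4.3.5.** Z = 1.96, P = 0.42, Q = 0.58, D = 2, sampling error 0.05, b = 40 women per cluster. From section 4.1: 40 parishes. From section 4.3.6: 21 parishes sampled.

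**The plan's own figure.** C = Z²PQD/(δ²b) = 1.96² × 0.42 × 0.58 × 2 / (0.05² × 40) = 18.72 clusters. Then 18.7 × 40 = 748 women, and 748 × 1.10 = 822.8, so 823 women; 823/40 = 20.6, so 21 clusters. All stated figures reproduce, and the factor of 2 for clustering is in them.

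**Implied outcome correlation.** D = 1 + (b − 1)ρ, so ρ = (2 − 1)/39 = 0.0256.

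**Prevalence intervals at P = 0.42, n = 748.**

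- Clustering ignored: 1.96 × √(0.42 × 0.58/748) = 3.5 points.
- With D = 2: 3.54 × √2 = 5.0 points, the planned sampling error.
- The naive interval is 1/√2 = 0.71 of the correct width. Its coverage is 1 − 2[1 − Φ(1.96/√2)] = 83%.
- At n = 823 the half-widths are 3.4 and 4.8 points.

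**With a first-stage finite population correction.** In units of PQ/n, the variance splits into a between-parish part of 40 × 0.0256 = 1.03 and a within-parish part of 1 − 0.0256 = 0.97. The correction is 1 − 21/40 = 0.475. The variance ratio becomes 0.475 × 1.03 + 0.97 = 1.46, ignoring any second-stage correction. The correct half-width is then 3.54 × √1.46 = 4.3 points, and naive coverage is about 89%.

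**Odds ratios.** D = 2 is a design effect for a prevalence. For an odds ratio, the variance ratio is approximately 1 + (b − 1) × ρ × ρx, where ρx is the parish intraclass correlation of the characteristic. Here (b − 1) × ρ = 39 × 0.0256 = 1, so the ratio is 1 + ρx. The actual two-sided error of a nominal 5% test is 2[1 − Φ(1.96/√ratio)]. The Protocol does not give ρx, so the values below are assumptions covering its whole range from 0 to 1. The last column is a beta-binomial simulation with 21 clusters of 39 women and 4,000 runs.

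| Assumed ρx | Variance ratio | False-positive rate | Simulated |
|---|---|---|---|
| 0 | 1.00 | 5.0% | 5.3% |
| 0.05 | 1.05 | 5.6% | 4.8% |
| 0.10 | 1.10 | 6.2% | 5.6% |
| 0.30 | 1.30 | 8.6% | 8.4% |
| 1 (constant within parish) | 2.00 | 16.6% | 15.8% |

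**The case against.** The strongest reply is that this is an omission and not a wrong method. Survey-design estimation also reports odds ratios and confidence intervals, and an individual unit of analysis is compatible with clustered standard errors. Nowhere does the Protocol say that women will be treated as independent, and a separate analysis plan, not shown, could name the variance estimator. This stands as far as it goes: a reader might infer that the plan commits to an independence analysis, and the text does not state that. But 4.3.8 is itself an analysis plan. It names the software and statistics and uses intervals as tests, while the clustering appears only in the sample size.

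A reader might also infer that the determinant tests will reject about 16.6% of the time. The documents do not support this. That figure needs a characteristic that is constant within a parish. The characteristics in Annex 6 (age, parity, education, marital status, occupation) belong to the woman and can vary within parishes, so the excess may be small or absent.

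Two further points stand. Section 4.3.8 mentions intervals only for the association step, so the 3.5 versus 5.0 point contrast applies only if prevalence intervals are reported. And no decision rule ties a significant odds ratio to an educational message; Annex 15 already lists the topics, and point estimates do not depend on the choice of standard error.

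**Conclusion.** The mismatch between design and analysis text is real, and its consequence is limited. Prevalence intervals that ignore clustering would be about 29% too narrow on the plan's own D = 2, and still too narrow, by a smaller margin, if the finite population correction is applied. For odds ratios no single inflation figure can be given: it runs from none to a ceiling of about 16.6%, and stays near 5% to 6% for characteristics that cluster weakly by parish. These results rest on D = 2 being right for the outcome, on about 40 women per parish, and on assumed covariate correlations. Because the inflation differs by characteristic and is unknown in advance, clustering should be handled routinely and not case by case. This is a minor correction to a formative survey.

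**What to change.** Add to section 4.3.8 that all prevalences, odds ratios and their confidence intervals will be computed with survey-design estimation in the named package. Parish should be the primary sampling unit, with sampling weights if selection probabilities turn out unequal, and a t reference with about 20 degrees of freedom (21 parishes less 1). A first-stage finite population correction for 21 of 40 parishes is optional and suits only statements that describe these two districts.

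The cost is a sentence of text, a few commands in Stata, and keeping the parish identifier in the data set. Sample size and fieldwork are unchanged. The downside is somewhat wider intervals.
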